### 4.4.3 Follow-up

Electronic patient self-reported scale (Jiangsu Rehn Medtech Technology Co., Ltd) will be applied to evaluate and record the occurrence of PONV in real time, including the time to each PONV and corresponding VAS score. The VAS is a simple-to-use measure to evaluate intensity of PONV. It’s a 10-point numerical rating scale with 0 = “no nausea or vomiting” and 10 = “worst nausea imaginable and vomiting”. The cut points on the PONV VAS have been recommended: mild PONV ( 4), which has little impact on daily activities and does not affect sleep; severe PONV ( 7), which results in inability to sleep and seriously hinders daily life; moderate PONV, whose clinical influence intervenes between the two above. When PONV happens at any time, patients or their caregivers spontaneously assess the severity of PONV with VAS and then send it to the central server through the electronic scale. The evaluator port harvests PONV information immediately so that it can be managed timely. To ensure a blinded fashion, both groups will be evaluated by direct questioning in the ward after 12 am at the 1st and 2nd postoperative day in ward. Persistent nausea was defined as continuous nausea lasting over 5 min. If the patients are discharged on the second day postoperative, they will be assessed by telephone. The postoperative 30-day information about delayed curative efficacy, complications and adverse events will be obtained through telephone follow-ups and electronic medical record system.

### 4.5 Summary table of chronology of research and examinations conducted

**Table 1. Clinical Research Process**

|  | **BOD**  **1** | **OD**  **OR** | **OD**  **PACU** | **POD**  **1** | **POD**  **2** | **POD**  **30** |
| --- | --- | --- | --- | --- | --- | --- |
| **preliminary screening** | √ |  |  |  |  |  |
| **Informed consent** | √ |  |  |  |  |  |
| **SAS** | √ |  |  |  |  |  |
| **Rescreening** |  |  | √ |  |  |  |
| **Randomization** |  |  | √ |  |  |  |
| **RASS** |  |  | √ |  |  |  |
| **Intervention** |  |  | √ | √ |  |  |
| **Evaluation** |  |  |  | √ | √ | √ |

√ : routinely performed, BOD 1: 1 day before operation, OD: operation day, OR: operation room, PACU: post anesthesia care unit, POD (1, 2, 30): (1, 2, 30) day after operation

### 4.6 Description of temporary stop rules

**Exit criteria:** The exit criteria includes the following: 1) patients who exit and terminate observation due to serious adverse events; 2) have other diseases and are unwilling to continue treatment; 3) want to exit for any reason not related to the study; 4) mistakenly included; 5) with poor compliance and unable to cooperate with the researchers to complete the intervention or cannot provide important assessment information.

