### 9. STATISTICAL ANALYSIS

**Sample size estimation and data analysis：**In previous studies, the PONV incidence was reported to be approximately 40%, and the PONV incidence was reduced by 7% with the TEAS treatment(19). With a significance set at 0.05, power set at 80%, the sample size required to detect differences was 742 patients in each group calculated with the Pass 11 software (NCSS, LLC. Kaysville, Utah, USA). Taking into account a loss-to-follow-up rate of about 10%, 1634 patients in total were enrolled to meet the minimum sample size requirement.

**Sample distribution:** Describes the size and loss rate of each data set, and provides detailed reasons for loss.

**Data comparability:** Preoperative baseline information, surgical information, anesthetic and antiemetic drug usage are compared between the two groups.

**Validity analysis:** The primary and secondary outcomes of the two groups are compared.

**Safety analysis:** Chi-square statistical tests are performed for the number and incidence of adverse events.

According to the intentionality analysis ITT principle, all subjects are included even if they have undergone in part of the trial process. At the same time, the efficacy and safety indicators will be included into the PP data set conformed to the schemed set, and then statistically analyzed in strict accordance with the scheme. Continuous variables will be described by means (SDs) and median (IQR), the differences between the two groups will be compared using the independent-sample T test. Categorical variables will be described by numbers (percentages), and chi-square test and Fisher's accuracy test will be used to test the incidence. Nonparametric rank sum test will be used for the grade data. *P value*<.05 will be considered statistically significant. All statistical analyses will be performed using SPSS software (version 25.0, IBM Corporation).

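### Section 4.6 ends observation for serious-adverse-event exits and provides no follow-up after other post-randomisation exits, in conflict with the all-subjects ITT rule and the 30-day safety follow-up

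*Protocol*

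**What the plan says.** Section 4.6 (Exit criteria) gives five grounds for exit. The first is "patients who exit and terminate observation due to serious adverse events". The second and third cover other illness with unwillingness to continue treatment, and voluntary exit. The fourth is mistaken inclusion. The fifth is patients "with poor compliance and unable to cooperate with the researchers to complete the intervention or cannot provide important assessment information". Only the first item says that observation ends. None says that an exited patient is still assessed.

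Under Prescreening and rescreening (section 4.3) and in Table 1 (section 4.5), randomisation takes place in the PACU, after extubation and a second eligibility check. Failure to complete the intervention is therefore always a post-randomisation event.

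Section 9 says of ITT that "all subjects are included even if they have undergone in part of the trial process". It adds that, at the same time, "the efficacy and safety indicators will be included into the PP data set". Section 8 has adverse events recorded from enrolment to 30 days after the operation, and section 4.4.3 plans 30-day follow-up by telephone and medical record.

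**The concern.** An all-randomised analysis needs an outcome for every randomised patient. The primary outcome (section 4.2.2) is any nausea, retching or vomiting in the first 24 h. If a patient leaves before that window has been checked, a reported episode still counts, but a patient with none reported cannot be confirmed free of PONV. A later analysis plan can choose how to handle a missing outcome; it cannot recover data that the protocol stopped collecting.

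Exits could differ by arm. TEAS is turned up to the most the patient tolerates, while Sham delivers no current (section 4.3.3). Section 4.6 does not say who judges compliance, and section 4.4.2 does not list the interveners among those blinded. Exits could also relate to outcome, since a nauseated patient may be less willing to finish a session. If both happen, the primary comparison is biased.

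For safety, a serious adverse event is the reason to keep observing a patient, not to stop, and a per-protocol set is the one most likely to lose such patients.

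**Working it through.** **1. The plan's own figures.** Inputs from section 9: "the PONV incidence was reported to be approximately 40%, and the PONV incidence was reduced by 7% with the TEAS treatment", significance 0.05, power 80%. Reading this as 40% against 33%, two-sided, with pooled variance under the null:

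n = [1.960 × √(2 × 0.365 × 0.635) + 0.842 × √(0.40 × 0.60 + 0.33 × 0.67)]² / 0.07² = 741.4, rounded up to 742.

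This matches "742 patients in each group calculated with the Pass 11 software". Then 742 × 1.10 = 816.2, rounded up to 817 per arm, or 1634 in total, which matches "Taking into account a loss-to-follow-up rate of about 10%, 1634 patients in total were enrolled". The plan thus allows for about 10% loss, and that sets the scale for the next step.

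**2. Possible bias in the primary comparison.** Let p be the true PONV rate, d the share of an arm whose 24 h outcome is lost through exit, and q the PONV rate among those lost. If the remaining patients are analysed:

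observed rate = (p − d × q) / (1 − d)

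The protocol gives neither d by arm nor q, so both are assumptions. Take no true effect (p = 40% in both arms), 817 randomised per arm, d = 10% in TEAS and 5% in Sham:

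| PONV among those lost (q) | TEAS observed | Sham observed | False TEAS benefit (points) | Chance of a significant result |
|---|---|---|---|---|
| 40% | 40.00% | 40.00% | 0 | 5% |
| 60% | 37.78% | 38.95% | 1.2 | 7.5% |
| 80% | 35.56% | 37.89% | 2.3 | 16% |
| 100% | 33.33% | 36.84% | 3.5 | 30% |

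The last row in full: (0.40 − 0.10) / 0.90 = 0.3333 and (0.40 − 0.05) / 0.95 = 0.3684. With about 735 and 776 patients left, the pooled standard error is about 0.0246, so z = 0.0351 / 0.0246 = 1.43, and the chance of exceeding 1.96 is about 30%.

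Three limits on this calculation:
- If d and q are the same in both arms there is no false difference. With d = 10% and q = 80% in both, each arm shows 35.6%.
- Equal exit rates are not enough if q differs. With d = 10% in both arms, q = 80% in TEAS and 40% in Sham, the rates are 35.6% and 40.0%, a gap of 4.4 points.
- If q is below 40% the sign turns. At q = 20%, TEAS shows (0.40 − 0.02) / 0.90 = 42.2% and Sham (0.40 − 0.01) / 0.95 = 41.1%, about 1.2 points against TEAS.

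**3. Safety, sections side by side.** Section 4.6 ends observation for serious-adverse-event exits; sections 4.4.3 and 8 require follow-up and event recording to 30 days. These cannot both be followed for the same patient. Section 9 has a safety paragraph with chi-square tests and no named set, then puts safety indicators into the per-protocol set alongside ITT. No arithmetic applies, because the protocol gives no expected rate of serious adverse events.

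**The case against.** Several stronger readings are tempting, and the protocol does not support them.

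- A reader might infer that observation ends for every exit. The text says so only for serious adverse events, and even that item can be read as describing patients who have stopped rather than as an instruction. For mistaken inclusion and poor compliance it is an inference from the word exit and from the absence of any stated follow-up. The last part of the fifth criterion describes an outcome that is already unobtainable.
- A reader might infer that patients with PONV vanish from ITT. Section 9 says the opposite, and section 4.4.3 has episodes sent to a server as they occur, so a patient who stops while vomiting has normally already met the endpoint. The outcomes left open are more often those with no episode yet, which could pull q down and turn the bias against TEAS. The second session also falls late in the 24 h window.
- The arm-dependent mechanism is plausible, not shown. Intensity is set to each patient's own tolerance, section 8 reports good tolerance, and vomiting can interrupt a Sham session too. Mistaken inclusion has no evident link to outcome.
- A reader might infer that safety is analysed per protocol only. Section 9 runs that set alongside ITT, and section 8 requires events to be recorded.

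All of this stands, and it rules out presenting any single bias figure as the expected error. It does not remove the conflict. A patient who exits over the PACU session leaves with most of the window ahead, and one who exits over the morning session leaves before the first direct questioning, which is scheduled after it. Rules for missing outcomes may sit in an analysis plan not at hand and are not counted as missing here; who stays under observation is fixed by the protocol.

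**Conclusion.** The point holds as a contradiction between section 4.6 on one side and sections 4.4.3, 8 and 9 on the other. Applied as written, section 4.6 can leave 24 h PONV status unconfirmed and can cut short the follow-up of patients with a serious adverse event. A per-protocol safety analysis may omit those same patients; that part needs no assumption about exit patterns.

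The effect on the primary comparison is conditional. With no true effect and assumed losses of 10% and 5%, the false benefit is 0 to 3.5 points for q from 40% to 100%, against a design effect of 7 points. It is zero if exit patterns are alike in both arms or unrelated to PONV, and it can run the other way. Treating the plan's 10% allowance as exits with lost outcomes is itself an assumption. This should be fixed, but it does not show that the primary result would be biased.

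**What to change.** Reconcile sections 4.6, 8 and 9:

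- In 4.6, separate stopping the intervention from leaving the study. This leaves untouched the question of when the intervention should stop, which is for the investigators.
- State that the PONV evaluations on postoperative days 1 and 2 and the 30-day adverse event follow-up continue for every randomised patient unless consent is withdrawn, including those with a serious adverse event, mistaken inclusion or incomplete sessions.
- In section 9, keep ITT (all randomised) as the main analysis and per protocol as supportive.
- Report safety in all patients who received at least one session, rather than in the per-protocol set.

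The cost is protocol wording plus the effort of following early stoppers. The ward visits, electronic scale and 30-day call already exist. There is a small gain in power: at 40% against 33%, it is 83.7% if all 1634 are analysed, compared with 79.7% if 10% are lost (1634 × 0.90 / 2 = 735 per arm).

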### 5. PATIENTS SELECTION AND EXCLUSION

### 5.1 Inclusion criteria

These criteria include the following: 1) selective laparoscopic non-gastrointestinal surgery under general anesthesia; 2) age 18–50 years old, BMI 15–40 kg/m2, ASA class I–III; 3) PONV risk prediction score Apfel ≥ 3 points; 4) ability to understand, sign informed consent and coordinate intervention and evaluation.

### 5.2 Exclusion criteria

These criteria include the following: 1) pregnancy and breast-feeding patients; 2) TEAS contraindications: skin allergy, breakage, infection or itching of test points, allergic to adhesive tape, pacemaker implanted; 3) history of alcohol, opioids or other drug abuse; 4) likely admission to ICU after surgery; 5) participation in other clinical studies within 3 months before admission to this study.

### 6. PERIOPERATIVE MANAGEMENT FOR PATIENTS

Attending anesthesiologists administrated PONV prophylaxis in operation room. Dexamethasone 5 mg IV and the second-generation 5-hydroxytryptamine 3 (5-HT3) receptor antagonists palonosetron 0.075 mg are administrated before anesthesia induction, or dexamethasone 5 mg and tropisetron 2mg are respectively administrated before anesthesia induction and at the end of surgery. Patients will be inducted with propofol (2 mg/kg), sufentanil (0.3 μg/kg) and cisphenyl sulfatracurium (0.15 mg/kg), and intubated. Anaesthesia maintenance will be performed using remifentanil (0.1 μg/kg/h), cisphenyl sulfatracurium (0.1 mg/kg/h), dexmedetomidine (initial dose 1 μg/kg for 10 min, maintenance dose 0.4 μg/kg/h) and sevoflurane (oxygen flow of 2 L/min and a dial setting of 1%) and/or propofol (4–8 mg/kg/h) as necessary to keep BIS 40-60 throughout surgery. All patients will receive identical multimodal analgesia in both arms to keep the postoperative pain numerical score less than 4 points. Patients will be rescued once PONV score >7. If it is not exceeded 6 h after the first 5-HT3 administration, propofol 20 mg IV or haloperidol 0.5–2 mg IV will be administrated. If it is exceeded 6 h after the first 5-HT3 administration, tropisetron 0.5 mg or ondansetron 2 mg IV will be administrated.

### 7. Data collected

The CRF table will be entered on Crabyter scientific research system (Xinyu Information Technology Co., Ltd), respectively by interveners and evaluators. It will include preoperative and postoperative screening forms, the informed consent form, anesthesia，antiemetic and analgesic record forms, postoperative intervention forms, postoperative evaluation forms, adverse event registration, exit registration forms, etc. Electronic patient self-reported scale (Jiangsu Rehn Medtech Technology Co., Ltd) was used to evaluate and record the occurrence of PONV, including time and corresponding severity. After completing the study, data administrator will retrieved all data in excel format. The postoperative 30-day complications and adverse events were obtained through telephone follow-ups and were stored in the electronic medical record system.

### 8. SAFETY ASSESSMENT

As TEAS are non-invasive, patients usually have a good tolerance, and the possible adverse reactions are mostly uncomfortable caused by electric stimulation, redness and swelling of electrode adhesion site, while very few patients may appear as hypoglycemia due to active gastrointestinal movement caused by acupoint stimulation. Most adverse reactions are mild and disappear after cease of electrical stimulation. No adverse reactions have been observed in the pre-experiment, and no serious adverse reactions have been reported in previous studies. If occurring from the day patients enrolled to 30 days after the operation, adverse events will be processed and recorded in time, and reported to the principle investigator as well as the director of ethics committee of the hospital in 24 h.

### 9. STATISTICAL ANALYSIS

**Sample size estimation and data analysis：**In previous studies, the PONV incidence was reported to be approximately 40%, and the PONV incidence was reduced by 7% with the TEAS treatment(19). With a significance set at 0.05, power set at 80%, the sample size required to detect differences was 742 patients in each group calculated with the Pass 11 software (NCSS, LLC. Kaysville, Utah, USA). Taking into account a loss-to-follow-up rate of about 10%, 1634 patients in total were enrolled to meet the minimum sample size requirement.

**Sample distribution:** Describes the size and loss rate of each data set, and provides detailed reasons for loss.

**Data comparability:** Preoperative baseline information, surgical information, anesthetic and antiemetic drug usage are compared between the two groups.

**Validity analysis:** The primary and secondary outcomes of the two groups are compared.

**Safety analysis:** Chi-square statistical tests are performed for the number and incidence of adverse events.

According to the intentionality analysis ITT principle, all subjects are included even if they have undergone in part of the trial process. At the same time, the efficacy and safety indicators will be included into the PP data set conformed to the schemed set, and then statistically analyzed in strict accordance with the scheme. Continuous variables will be described by means (SDs) and median (IQR), the differences between the two groups will be compared using the independent-sample T test. Categorical variables will be described by numbers (percentages), and chi-square test and Fisher's accuracy test will be used to test the incidence. Nonparametric rank sum test will be used for the grade data. *P value*<.05 will be considered statistically significant. All statistical analyses will be performed using SPSS software (version 25.0, IBM Corporation).

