**GENERAL INFORMATION**

# 1. SUMMARY

**Introduction:** Postoperative nausea and vomiting (PONV) is among the most common postoperative complications, which gives patients extremely afflictive medical experience and sometimes intractable side-effect, leading to prolonged hospitalization, increased medical expenses and lower surgical satisfaction. PONV prophylaxis has been included in enhanced recovery after surgery (ERAS) management strategy. Even though the incidence of PONV can be decreased by using less of opioid and inhalational anesthetics and/or using antiemetic drugs, its occurrence is still high up to 20% in high-risk patients. Complementary to the antiemetic drugs, non-pharmacotherapy acupuncture treatment, represented by transcutaneous electrical acupoint stimulation (TEAS), has been used to prevent PONV occurrence. However, its effectiveness in preventing PONV has not been established yet due to small sampling size and not well controlled in the previous studies.

**Hypothesis:** TEAS treatment based on standardized antiemetic prophylaxis significantly lowers PONV incidence than the Sham treatment.

**Primary outcome:** PONV incidence

**Secondary outcomes:** PONV quantitative indicators including the time and VAS score of first nausea and vomiting, the times and VAS scores of each nausea and vomiting within 24 h after surgery; ERAS items including the 40-item Quality of Recovery (QoR-40) within 24 h, PONV related complications.

**Methods:** A multicenter, prospective, evaluator-blinded, parallel-group, randomized controlled trial (RCT) is administered in Sham or TEAS treatment on laparoscopic non-gastrointestinal surgery patients.

**Number of patients:** The number of patients to be included 1655 cases in total.

**Inclusion criteria:** 1) selective laparoscopic non-gastrointestinal surgery under general anesthesia; 2) age 18–50 years, BMI 15–40 kg/m2, ASA class I–III; 3) Apfel score ≥3 points; 4) ability to understand, sign informed consent and coordinate intervention and evaluation.

**Exclusion criteria:** 1) pregnancy and breast-feeding patients; 2) TEAS contraindications: skin allergy, breakage, infection or itching of test points, allergic to adhesive tape, pacemaker implanted; 3) history of alcohol, opioids or other drug abuse; 4) likely admission to ICU after surgery; 5) participation in other clinical studies within 3 months before admission to this study.

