# 4. RESEARCH DESIGN

# 4.1 Type of study

This work is a multicenter, prospective, evaluator-blinded, parallel-group, RCT. Using Crabyter scientific research system (Xinyu Information Technology Co., Ltd), the enrolled patients will be randomly divided into Sham and TEAS groups in a 1:1 ratio, with four patients regarded as a block, and obtain the random number.

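### The planned total is given as 1634 in Section 9 and 1655 in the Summary; 1634 inflates by 1.10 instead of dividing by 0.90 and misses the required 742 per group

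*Protocol*

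**What the plan says.** Section 9 (Statistical Analysis) sets out the calculation. For the control rate, "the PONV incidence was reported to be approximately 40" per cent. For the effect, "the PONV incidence was reduced by 7% with the TEAS treatment". For the error rates, "With a significance set at 0.05, power set at 80" per cent. From these it concludes that "the sample size required to detect differences was 742 patients in each group". It then allows for dropout: "Taking into account a loss-to-follow-up rate of about 10%, 1634 patients in total were enrolled to meet the minimum sample size requirement".

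Section 1 (Summary) gives a different total: "The number of patients to be included 1655 cases in total". No derivation accompanies it, and nothing elsewhere in the protocol links it to 1634.

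Section 4.1 fixes the allocation: patients are "randomly divided into Sham and TEAS groups in a 1:1 ratio", in blocks of four.

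**The concern.** There are two separate faults.

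First, the protocol states two totals, 21 patients apart, each presented as the size of the trial. Nothing says that one is a minimum and the other a target. Apart from the recruitment window in Section 4.3.1, the protocol describes no other rule for ending enrolment, and Section 4.4.1 has the centres competing to fill shared blocks. Stopping at 1634 or at 1655 could each be called compliant, and the number finally enrolled could not be checked against a single prespecified figure.

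Second, the Section 9 total looks like the common dropout slip of adding 10% to the evaluable number when it should be divided by the 90% expected to remain. If so, the sentence claiming that 1634 meets the minimum is not true at the loss rate it assumes.

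**Working it through.** **Inputs (Section 9, with 1:1 allocation from Section 4.1).** p1 = 0.40; p2 = 0.33; alpha = 0.05; power = 0.80; loss = 10%. Section 9 does not say whether the 7% is absolute or relative, or whether the test is one- or two-sided. An absolute reduction with a two-sided test is the reading that returns 742, so it is used here.

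**Step 1: reproduce 742.** The pooled-variance formula for two proportions, without continuity correction, is

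n = [z(0.975)·√(2·p̄·(1−p̄)) + z(0.80)·√(p1(1−p1) + p2(1−p2))]² / (p1−p2)²

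with p̄ = 0.365:

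- first term: 1.960 × √0.46355 = 1.3344
- second term: 0.8416 × √0.4611 = 0.5715
- n = (1.9059)² / 0.0049 = 741.3, rounded up to **742 per group**, as stated.

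Other readings do not match: one-sided gives 584, continuity-corrected 770, unpooled 739, arcsine 741, and 7% read as relative (0.40 versus 0.372) gives 4745.

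**Step 2: reproduce 1634.**

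- 742 × 1.10 = 816.2, rounded up to 817; 817 × 2 = **1634**, an exact match.
- 742 / 0.90 = 824.4, rounded up to 825; 825 × 2 = **1650**.

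So 1634 comes from multiplying by 1.10. It is 16 patients (1.0%) below the figure obtained by division.

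**Step 3: apply the stated 10% loss to each total.** Power is from the same formula, solved for power.

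| Total | Evaluable (× 0.90) | Per group | Power | Largest loss that still leaves 1484 |
|---|---|---|---|---|
| 1634 (Section 9) | 1470.6 | 735.3 | 79.7% | 9.2% |
| 1650 (742/0.90) | 1485.0 | 742.5 | 80.1% | 10.1% |
| 1655 (Summary) | 1489.5 | 744.75 | 80.2% | 10.3% |

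The last column is 1 − 1484/N, where 1484 = 2 × 742. Power at exactly 742 per group is 80.0%.

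**Step 4: try to derive 1655.** It is neither 2 × 817 = 1634 nor 2 × 825 = 1650. It is also odd, so it cannot split equally under 1:1 allocation. The documents do not show where it comes from.

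**The case against.** The strongest reply is that the numerical effect is negligible. The protocol assumes loss of about 10%, not exactly 10%, and 1634 is sufficient if loss is no more than 9.2%. At exactly 10% the cost is about 0.3 percentage points of power, which is small beside the uncertainty in a control rate given only as approximately 40%. Patients are randomised after extubation (Section 4.3), the primary outcome is complete within 24 hours (Section 4.2.2), and Section 9 calls for an intention-to-treat analysis, so true loss for the primary outcome may well be below 10%. One of the two stated totals, 1655, does meet the requirement.

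All of this stands as a limit on weight. It does not remove either fault: no loss rate in the protocol reconciles 1634 with 1655, and the Section 9 sentence fails on the rate it states.

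It might also be said that 1634 is a floor, or a report of actual enrolment, since Section 9 uses the past tense. The protocol does not call it a floor, and the exact match to 2 × 817 shows a planning figure.

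Two practical points are fair. The 1650 does not appear in the protocol, and it is not a multiple of the block size (1650/4 = 412.5). The same is true of 1634 (408.5) and 1655 (413.75), so block size does not favour either stated figure.

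**Conclusion.** The point holds. The protocol gives two unexplained totals, and the Section 9 total falls short of its own requirement: about 735 per group after 10% loss, against 742. The size is modest: 16 patients below the correctly inflated 1650, 21 below the Summary figure, and 79.7% power instead of 80.0%. This is a fault of arithmetic and consistency in the stated target and does not threaten the validity of the trial. Only 1634 misses the requirement; 1655 satisfies it but is underived.

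The shortfall rests on taking loss as exactly 10%, equal in both groups, with lost patients contributing nothing to the primary analysis. It disappears if loss is 9.2% or lower. The conflict between the two totals rests on no assumption.

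**What to change.** State one total, with its derivation, in both Section 1 and Section 9. The direct correction is to replace 1634 in Section 9 with 742/0.90 = 824.4, rounded up to 825 per group and 1650 in total, and to align the Summary to it. If the sponsor prefers 1655, Section 9 should adopt that figure and say how it was reached. If 1634 is kept, the Summary should be changed to match, and Section 9 should state an expected evaluable size of 735 per group with 79.7% power and drop the claim that the minimum is met at 10% loss.

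When Section 9 is edited, say also that the 7% is an absolute difference and that the test is two-sided, since 742 depends on both.

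The cost is wording only. Relative to the Summary's 1655 no patients are added; relative to Section 9's 1634, moving to 1650 adds 16.

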# 4.2.2 Primary outcome

In this study, at least once nausea, retching or vomiting after operation, or any combination of the above symptoms within 24 h after surgery is taken as the diagnostic criteria of PONV, thereby setting PONV incidence 24h as a primary outcome.

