# 4.2.3 Secondary outcome

Secondary research indicators are PONV quantitative indicators and ERAS-related items. PONV quantitative indicators include the time and visual analogue scale (VAS) score of first PONV, the cumulative times and the highest VAS score of nausea and vomiting within 24 h after surgery. ERAS items include the 40-item Quality of Recovery (QoR-40) within 24 h, PONV related complications and postoperative hospital stay. The specific contents of QoR-40 score include five aspects: physical comfort (12 items, 60 scores), emotional state (9 items, 45 scores), physical independence (5 items, 25 scores), psychological support (7 items, 35 scores) and pain (7 items, 35 scores)(21). PONV related complications are dizziness and headache, electrolyte imbalances and pain.

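### Time of first PONV falls to a t test although only patients with PONV have a value, so the comparison is made in outcome-selected subgroups and can mislead; first-episode VAS shares the selection problem

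*Protocol*

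**What the plan says.** Protocol section 4.2.3 lists as secondary outcomes "the time and visual analogue scale (VAS) score of first PONV, the cumulative times and the highest VAS score of nausea and vomiting" over 24 h. Section 4.4.3 explains how these values arise: "When PONV happens at any time, patients or their caregivers spontaneously assess the severity of PONV with VAS". A patient with no episode therefore produces neither a time of first PONV nor a first-episode score. Section 4.2.2 fixes the window, in that a qualifying symptom "within 24 h after surgery is taken as the diagnostic criteria of PONV".

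Section 9 states that "The primary and secondary outcomes of the two groups are compared", without a method for each outcome. It gives three general rules:
- continuous variables: "the differences between the two groups will be compared using the independent-sample T test";
- categorical variables: chi-square or Fisher's test;
- graded data: "Nonparametric rank sum test will be used for the grade data".

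On the analysis set, it says under the ITT principle that "all subjects are included even if they have undergone in part of the trial process". It mentions no survival method and no censoring, and it assigns no value to patients without PONV in the first-episode outcomes.

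**The concern.** Time of first PONV is continuous, so the only rule in section 9 that fits it is the t test. That test can use only patients with an event. Having an event is the primary outcome, which TEAS is meant to change, so the two groups compared are no longer the randomised groups. Patients who stayed free of PONV for 24 h carry the most favourable information about time, and they contribute nothing.

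What is at stake is how a reported secondary result reads. If TEAS removes mainly later episodes, the remaining TEAS episodes are on average earlier. The t test may then suggest that TEAS brings PONV forward, although no patient's first episode came sooner. If TEAS removes episodes regardless of timing, the test sees almost nothing and a real benefit goes unreported.

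**Working it through.** **1. Inputs.** Section 9: Sham incidence 40%, a reduction of 7%, alpha 0.05, power 80%, 742 per group. Section 4.2.2: 24 h window. The documents give no distribution of event times or VAS scores, so those below are assumptions.

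**2. The plan's own figure.** Read 7% as absolute (40% vs 33%), two-sided, pooled variance, mean rate 0.365:

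n = [1.96·√(2·0.365·0.635) + 0.8416·√(0.40·0.60 + 0.33·0.67)]² / 0.07² ≈ 741.3, so 742 per group. The stated figure is reproduced and the rates can be used.

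**3. Who has a value.** Sham: 742 × 0.40 = 296.8. TEAS: 742 × 0.33 = 244.9. Together that is about 542 of 1,484 (36.5%). The other 63.5% have no first-episode time or VAS.

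**4. Timing assumption A.** First-event times are exponential with mean 6 h, truncated at 24 h. TEAS prevents 45% of events after 6 h and none before.
- Share of events after 6 h: (e⁻¹ − e⁻⁴)/(1 − e⁻⁴) = 0.356.
- TEAS incidence: 0.40 × (1 − 0.45 × 0.356) = 33.6%.
- Mean time among cases, Sham: 6 − 24e⁻⁴/(1 − e⁻⁴) = 5.55 h.
- Mean time among cases, TEAS: mean times before and after 6 h are 2.51 h and 11.06 h, so (0.644 × 2.51 + 0.356 × 0.55 × 11.06)/(0.644 + 0.356 × 0.55) ≈ 4.50 h.
- Simulated at 742 per arm, the t test is significant against TEAS in about 74% of trials.
- If prevention is instead unrelated to timing, the t test is significant in about 5% of trials over both directions, or about 2.5% each way. That is chance level.

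**5. Timing assumption B.** 60% of the Sham cumulative hazard falls in the first 6 h. Incidence is 40% vs 33% in every row; 742 per arm, 3,000 runs. Log-rank uses all randomised patients, censored at 24 h.

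| Effect of TEAS | Mean time in cases, TEAS vs Sham (h) | t test significant, TEAS earlier | t test significant, TEAS later | Log-rank favours TEAS |
|---|---|---|---|---|
| Proportional hazards | 7.07 vs 6.86 | 1.0% | 5.7% | 79.6% |
| Prevents later episodes only | 5.26 vs 6.88 | 86.4% | 0% | 65.9% |
| Prevents early episodes only | 8.33 vs 6.88 | 0% | 69.4% | 87.6% |

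**6. VAS of first PONV.** Assume case scores roughly normal with mean 4.5 and SD 2, limited to 1–10 (2,000 runs).
- Prevention unrelated to severity: case means are 4.53 and 4.53, so there is no case-only difference. A rank sum test in all patients, with 0 for no PONV, favours TEAS in 78% of runs.
- Only mild episodes (VAS 4 or less) prevented: case means are 4.87 (TEAS) and 4.53 (Sham), and the case-only t test is significantly worse for TEAS in 54% of runs. Rank sum in all patients favours TEAS in 58%.

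**The case against.** The t-test sentence is a general line that covers baseline, anaesthetic and outcome variables alike. It does not name time of first PONV, and rules for single outcomes are often left to the SAP, which is not shown. That explains the gap but does not remove it. The protocol says the secondary outcomes are compared, and it fixes one test for continuous variables that does not suit this one.

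Some stronger readings are tempting, and the documents do not support them:
- **That the plan says event-free patients are dropped.** It does not; its ITT statement says the reverse. Their omission follows from applying a t test to a quantity they do not have.
- **That VAS of first PONV will certainly be t-tested.** Section 4.4.3 gives mild, moderate and severe cut points, so VAS may fall under the rank sum rule for graded data. A rank sum test in cases only would have the same selection problem. Censoring applies to time, not to VAS.
- **That reversal is to be expected.** It needs TEAS to act mainly on later episodes. Section 4.3.3 places one session in PACU and one the next morning, which neither establishes nor excludes that pattern. Under proportional hazards there is essentially no reversal.
- **That the opposite pattern yields a false benefit.** When only early episodes are prevented, log-rank in all patients also favours TEAS. The t test agrees with a real benefit in direction. What would be wrong is to read the later mean as a delay in individual patients.

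**Conclusion.** The point holds for time of first PONV. The rule in section 9 leads to a comparison of about 297 with 245 patients selected by the primary outcome, and it cannot be squared with the ITT statement. For VAS of first PONV the selection problem holds whichever of the two tests is meant.

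The size of the distortion rests on assumed timing. The t test is significant against TEAS in about 1 to 2.5% of trials when prevention is unrelated to timing, and in about 74 to 86% when only later episodes are prevented. It is significant for TEAS in about 69% when only early episodes are prevented, under assumption B. No single figure from this range should be taken as the expected result. In the neutral case the main cost is a missed effect: about 6% of runs favour TEAS, against about 80% with log-rank.

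A reader might take this as a threat to the trial's main conclusion. It is not: the primary incidence comparison and the 742 per group are untouched. This should be fixed, but it is not critical.

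**What to change.** Amend section 9 to give these outcomes their own rules:
- Time to first PONV: all randomised patients, Kaplan-Meier curves with a log-rank test or Cox model, event-free patients censored at 24 h or at last contact if earlier.
- Severity: highest VAS within 24 h, already listed in section 4.2.3, compared in all randomised patients by rank sum, with 0 for patients without PONV. The scale in section 4.4.3 already defines 0 as the absence of nausea and vomiting.
- Time and VAS of first PONV among affected patients: descriptive only, without a p value, and labelled as conditional on having had PONV.

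The cost is a change of analysis wording. The electronic scale already records the time and score of each episode (sections 4.4.3 and 7), so no new data and no change in sample size are needed.
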